### 6.3 Target number of subjects and its estimation basis

#### 6.3.1 Number of subjects

We are planning to enroll 33 subjects per group that is suitable for inclusion/exclusion criteria and analyze final group of 31 subjects.

|                                                      | Futhan group | No-anticoagulation group | Total subjects |
|------------------------------------------------------|--------------|--------------------------|----------------|
| Validity assessment subjects                         | 31           | 31                       | 62             |
| Validity assessment subjects including drop-out (5%) | 33           | 33                       | 66             |

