### 6.3.2 Estimation basis

Primary end point of this clinical study is to evaluate the mortality of Futhan group and compare it to mortality of no-anticoagulation group.

Generally, the mortality of CRRT patients in ICU is known to be roughly 50% [1,4,5].

Thus, we anticipate the mortality in futhan group as 50% and assume the tolerance as 15% to estimate actual mortality. Also, we will add the same number of no-anticoagulation subjects to compare with futhan group on mortality.

Level of significance, ( $\alpha = 0.1$ )

Allowable limits of error for mortality are 15%. ( $\delta=0.15$ )

Considering the patient's severity in ICU, wastage rate is set at 5%. ( $r = 0.05$ )

Hence, necessary number of subjects is calculated after the following formula;

$$n_t = \frac{Z_{1-\alpha/2}^2 p(1-p)}{\delta^2}$$

By this formula, we estimate necessary number of subjects and calculate the final number of subjects by considering drop-out rate using the following formula.

$$n = \frac{n_t}{1-r}$$

The necessary number of subjects is 31 patients per group, and considering the 5% drop out rate, the final number would be 33 patients per group.

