#### 7.4.2 Medication that are prohibited to use in combination

The medications listed as following are not allowed to use in combination with nafamostat mesilate.

- ① Medication in similar effect: warfarin, urokinase, FOY, aprotinine, dextrin, prostaglandine etc.

② Anticoagulation medication: heparin, citrate, hirudine etc.

When the patient is needed to use medication that are prohibited to use in combination with nafamostat mesilate under researcher's approval, the patient is excluded from the study immediately and an accurate and detailed documentation should be noted at the last page of the clinical report.

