## 10. Study discontinuation, drop out, or analysis exclusion criteria

## 10.1 Study discontinuation and drop out criteria

All patients who enrolled in the study should be recorded of the completion of the study, and if the medication is discontinued or observation is stopped, the reason is recorded. The criteria for patient's drop-out are as follows.

- ① Circumstance that violates inclusion/exclusion criteria
- ② Serious adverse events occurred in patients or patients demands to be dropped out of the study due to adverse events.
- ③ Patient or legal guardian demand the discontinuation of the study due to unsatisfactory curative value during the study.
- ④ Severe hemorrhage
- ⑤ Critical violation of study protocol by principal investigator, researcher or patients.
- ⑥ Patients or legal guardian's withdrawal of the consent.
- ⑦ When patients cannot be followed.
- ⑧ When the patient takes a medication that can influence the study result, without the researcher's authorization during study period.
- ⑨ When the patient is decided not fit for the study progression by researchers.

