#### (4) Serious AE/ADR

Serious AE/ADR is adverse event or adverse drug reaction that has occurred in any dosage of medication during the clinical study, and is as follows;

- ① Patient's death during the study
- ② Life threatening circumstances (when the patient is exposed to the risk of death by the incidence of reaction)
- ③ When persistent or significant disability or functional deterioration is anticipated.
- ④ When the patient is need to hospitalized or prolong hospitalization period in already hospitalized patient
- ⑤ When causes congenital disability or abnormality
- ⑥ Other medically significant circumstances

Even if it is not listed above, when patient's safety or health is thought to be compromised, under supervision of attending physician and related specialist's opinion, the reaction is considered as serious adverse event and appropriate management is followed accordingly.

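### The 5% wastage behind 31 evaluable patients per group does not fit the per-protocol set it feeds, because serious adverse events are drop-out grounds and nothing says that deaths stay in that set

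*Protocol*

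**What the plan says.** Section 6.3.2 sizes the trial by the precision of one proportion. It states "we anticipate the mortality in futhan group as 50"%, "Allowable limits of error for mortality are 15"% and a significance level of 0.1, and says that the "wastage rate is set at 5"%. The result is 31 per group, raised to 33. The control group is given the same number. Section 6.3.1 and the synopsis repeat these figures, and 6.3.1 undertakes to "analyze final group of 31 subjects" per group.

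The set that receives this number is fixed in section 11.3.1. Efficacy is analysed principally per protocol, in patients who completed the protocol successfully. An intention-to-treat analysis of patients with confirmed vital status is additional.

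Several sections bear on who leaves the study or the analysis:

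- **10.1** lists nine drop-out grounds. One reads "Serious adverse events occurred in patients or patients demands to be dropped out of the study due to adverse events", and another is severe hemorrhage.
- **12.1 (4)** puts the patient's "death during the study" first in its list of serious events.
- **8.3.3** words a subject's death as discontinuation of the study. **14.10** says that the study is discontinued when a serious adverse event occurs.
- **7.4.2** says that if a prohibited drug is needed, "the patient is excluded from the study immediately".
- **10.2** gives a shorter list of grounds for disregarding data: missing consent, an eligibility violation or a prohibited drug. Minor violations are reviewed for inclusion in the per-protocol analysis.

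**The concern.** An allowance for wastage has to match the set that will be analysed. If efficacy needs only vital status at ICU discharge in a single centre, 5% is not contradicted by anything in the protocol. If it needs successful completion of the protocol, the 5% must also cover every patient who leaves under 10.1 or 7.4.2. The trial enrols hemodynamically unstable ICU patients who need renal replacement and have a bleeding tendency. In them, serious events and hemorrhage are to be expected, and death is the primary endpoint.

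The 31 evaluable patients and the 15-point limit are the only quantitative justification in the protocol, which states no power or detectable difference. If the per-protocol set is smaller than 31, the report will claim a precision that the analysed set lacks. If patients leave the set because they died, the mortality estimate itself is distorted.

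**Working it through.** **Inputs.** From section 6.3.2: α = 0.1, used two-sided in the protocol's formula (Z = 1.645); p = 0.50; δ = 0.15; r = 0.05.

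**1. The protocol's own figures.**

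n_t = Z² p(1 − p)/δ² = 1.645² × 0.25/0.0225 = 30.06, rounded up to 31.

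n = 31/(1 − 0.05) = 32.6, rounded up to 33.

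Both figures reproduce exactly, so there is no arithmetic error.

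**2. How much loss the figures tolerate.** The half-width of the 90% interval at p = 0.5 is 1.645 × √(0.25/m), where m is the number evaluable per group.

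| Loss from 33 (assumed) | m | Half-width (points) |
|---|---|---|
| none | 33 | 14.3 |
| 2 patients (6%) | 31 | 14.8 |
| 3 patients (9%) | 30 | 15.02 |
| 10% | 29 | 15.3 |
| 20% | 26 | 16.1 |
| 30% | 23 | 17.2 |

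For the percentage rows, m is rounded down to whole patients. Two losses keep the 31. Three losses miss the 31 and bring the half-width to the 15-point limit, marginally past it. The protocol gives no rate for non-fatal serious events, severe hemorrhage or prohibited drugs, so the rates in the table are assumptions, not predictions.

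**3. Do deaths leave the per-protocol set?** Set side by side, the sections do not settle this.

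- *Toward removal:* death is a serious event (12.1), a serious event is a drop-out ground (10.1), death is worded as discontinuation (8.3.3), and the per-protocol set needs successful completion (11.3.1).
- *Toward retention:* death is not itself one of the nine grounds in 10.1. It is also absent from the list of grounds for disregarding data in 10.2. ICU and hospital stay are measured to discharge or death (11.2.2), and ICU mortality is the primary endpoint (11.1.1).

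No sentence resolves it.

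**4. What removal of deaths would do.** Let true mortality be the planned 50%. Suppose a fraction f of the deaths is removed and no survivors are. Mortality in the remaining set is 0.5(1 − f)/(1 − 0.5f). As an illustration, f = 0.5 gives 0.25/0.75 = 33%, and f = 1 gives 0%. At f = 0.5 the shift is about 17 points, already more than the 15-point limit. Enrolling more patients does not change it.

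**The case against.** The strongest reply is that 10.2, not 10.1, governs exclusion from analysis, and that its list contains neither serious events, nor hemorrhage, nor death. A principal analysis of ICU mortality with almost no deaths in it can hardly be what the drafters intended. If deaths count as completed observations, 5% could be tenable.

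Much of this stands. It means that the protocol cannot be read as certainly removing deaths. It does not close the gap, because 11.3.1 defines the per-protocol set by successful completion and not by reference to 10.2. Nor does any text say that a patient who left under 10.1 has completed. Even on the narrow reading, 10.2 and 7.4.2 remove patients who receive a prohibited drug although their vital status is known.

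Three stronger readings are tempting, and the documents do not support them:

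- *About half of each group will be lost.* A reader might infer this by chaining 50% mortality to the drop-out rules. It is not a stated rate, and deaths in ICU after renal replacement has ended might not count as drop-outs. Precision or enrolment figures worked out at p = 0.5 for such a set would not describe it either, since a set without deaths has mortality near zero.
- *The limit fails in any analysis set.* It does not. Counting everyone with known vital status gives at most ±14.3 points at 33 per group and ±14.8 at 31, both inside the limit.
- *Two spare patients per group are too few even at a true 5% loss.* Dividing by (1 − r) targets the expected number evaluable. Chance variation around it is common to all such allowances and is no fault of this plan.

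**Conclusion.** The point holds as an inconsistency between the wastage assumption and the principal analysis set, not as a calculation error. For the per-protocol set as worded, the protocol supports neither 31 evaluable per group nor the 15-point limit.

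The effect on precision is modest over a plausible range: from 15.02 points at 9% loss to about 17.2 at 30%, taking p = 0.5 and a 90% interval. These figures rest on assumed loss rates and on losses unrelated to outcome.

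The more serious possibility is that deaths are treated as drop-outs, which would bias the principal mortality estimate toward zero. The text neither establishes nor excludes this, so sections 6.3, 8.3.3, 10.1, 10.2, 11.3.1, 12.1 and 14.10 must be reconciled. All of these are fixed in the protocol, so the conflict is more than a detail left for an analysis plan. It should be corrected.

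**What to change.** 1. In 6.3.1, 6.3.2 and the synopsis, define wastage as patients whose vital status cannot be established.
2. In 6.3 and 11.3.1, state that death is an endpoint and not a drop-out. State also that all other randomised patients, including those who stop the assigned treatment, count toward the mortality estimate.
3. State the resulting precision: ±14.3 points at 90% with 33 per group, and ±14.8 with 31.
4. If the per-protocol set stays principal, restate the evaluable number and the error limit at a wastage consistent with 10.1, and say whether patients who die or stop for a serious event belong to that set.

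The cost is wording in these sections. If per protocol is kept, the stated precision will also be less favourable. No extra patients are needed. No change to any clinical discontinuation rule is proposed; the request is only that those sections be made consistent with the mortality endpoint.

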## 7. Clinical study method

## 7.1 Clinical study design

This study is single center, randomized, open clinical study to compare mortality, patients' recovery, safety using nafamostat mesilate and no-anticoagulation during CRRT in ICU patients who has hemorrhagic tendency that prohibits usage of heparin.

When ICU patients with hemorrhagic tendency that needs CRRT who fits inclusion/exclusion criteria voluntarily agrees to participate in the study, patients who fit the inclusion criteria by subject compatibility result are randomly assigned to each group. Since CRRT duration can be different due to patient's condition, nafamostat mesilate administration will be continued until CRRT is discontinued. Afterwards, mortality after 28 days of CRRT discontinuation and renal recovery at 1st outpatient department visit will be compared between each group.

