| Study Duration                 | Patients were enrolled 12 months after IRB approval                                                                                                                                                                                                                                                                                                                             |
| Subjects                       | Patients who are in need of CRRT in ICU setting with a bleeding tendency that prohibits use of heparin.                                                                                                                                                                                                                                                                         |
| End Point                      | 
 
· Primary End Point
Mortality in ICU
 
· Secondary End Point
Comparison of efficacy and safety in two method during CRRT by comparing in-hospital mortality, mortality after 28 days after CRRT, CRRT duration, ICU period, in-hospital period, survival Time, filter life span, Blood loss, Transfusion, etc.
 
 |
| Phase & Design                 | Phase IV
Randomized, parallel phase IV clinical study                                                                                                                                                                                                                                                                                                                        |
| Study Drug                     | Futhan (nafamostat mesilate)                                                                                                                                                                                                                                                                                                                                                    |
| Dosage & Administration Method | IV futhan 50mg 1 vial was dissolved with 15 mL of 5% glucose solution. Futhan was initiated with a dose of 20 mg/hr, which was adjusted between 10 to 30 mg/hr under strict supervision of researchers. For priming, 2 vials of futhan was dissolved in 2mL of 5% glucose solution and injected to 500mL normal saline bag. This fluid was used to IV futhan                    |

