## ■ Study Protocol Summary

|                     |                                                                                                                                                                                                                                                                                                                                                                                                                                                                                                                                                                                                                                                                                                                              |
|---------------------|------------------------------------------------------------------------------------------------------------------------------------------------------------------------------------------------------------------------------------------------------------------------------------------------------------------------------------------------------------------------------------------------------------------------------------------------------------------------------------------------------------------------------------------------------------------------------------------------------------------------------------------------------------------------------------------------------------------------------|
| Method              | 
This study is a single-center, randomized, open clinical study to evaluate mortality, patients' recovery rate, safety between nafamostat mesilate group and no-anticoagulation group in patients who are prohibited from using heparin.
 
When the ICU patient who has hemorrhagic tendency and in need of CRRT voluntarily agrees to participate in the clinical study, the patients who are suitable by inclusion criteria are randomly assigned to each group. Nafamostat mesilate will be administered until CRRT is ceased due to various reasons, and after which patients mortality within 28 days after CRRT initiation and renal functional recovery at 1st outpatient department follow up.
 |

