| Validity assessment | 
 
· primary end point: mortality within ICU
 
· secondary end point               
 
① In-hospital mortality
 
② Mortality within 28 days after initiation of CRRT
 
③ CRRT duration
 
④ ICU hospitalization period
 
⑤ Total hospitalization period
 
⑥ Survival
 
⑦ Filter life span
 
⑧ Blood loss
 
⑨ transfusion
 
 
 
                                                                                                                                                                                                                                         |
| Safety assessment   | Adverse events, clinical pathology examination (hematologic, blood coagulation test, lipid exam, urine analysis)                                                                                                                                                                                                                                                                                                                                                                                                                                                                                                                                                                                                             |

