7: The patients were followed until discharge for mortality to confirm survival until 28 days after initiation of CRRT.

8: After discontinuation of CRRT, patients were followed at discharge to confirm dialysis maintenance and at first outpatient department follow-up after discharge, renal functional restoration was checked.

9: Free frozen plasma, platelet transfusion was checked during CRRT.

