### 8.3.4 Follow-up

Follow-up investigation includes recovery of renal function, patients' mortality. When patient's condition is improved and CRRT is not necessary, patient is followed whether he or she is on dialysis at discharge, and renal recovery is sought at 1st outpatient department visit after discharge. Also, mortality at discharge and 28 days after initiation of CRRT is investigated. Follow-up investigation is conducted according to patient's outpatient department visit schedule and no extra-visit for the study is planned.

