#### 11.1.2 Secondary validity assessment variables

- ① Mortality in hospital
- ② Mortality at 28 days after initiation of CRRT
- ③ CRRT duration
- ④ Hospitalization period in ICU
- ⑤ Hospitalization period
- ⑥ .Survival period
- ⑦ Filter life span
- ⑧ Blood loss
- ⑨ Transfusion

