#### 11.2.2 Secondary validity assessment variables

(1) Mortality in hospital

We will check whether the patients' mortality in hospital after CRRT is 50%, and additionally whether there is any statistical significant difference between two groups.

(2) Mortality at 28 days after initiation of CRRT

We will check whether the patients' mortality at 28 days after initiation of CRRT is 50%, and additionally whether there is any statistical significant difference between two groups.

(3) CRRT duration

We will check the duration of CRRT at ICU between the two groups.

(4) Hospitalization period in ICU

We will check the patients' duration within ICU until recovery to general ward or death.

(5) Hospitalization period

We will check the patients' duration within hospital until discharge or death.

(6) Survival period

We will calculate the survival 28 days after CRRT in both groups. Each patient's survival period is sought to calculate median survival time.

(7) Filter life span

We will check each filter life span during CRRT when CRRT is discontinued and calculate average filter life span.

(8) Blood loss

We will check blood loss at filter change during CRRT.

(9) Transfusion

We will check the amount of transfusion during CRRT.

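### Section 7.1 counts 28-day mortality from the end of CRRT while the endpoint definitions count from its start, and the follow-up text does not secure day-28 status after discharge

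*Protocol*

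**What the plan says.** On the time origin, the protocol has three kinds of statement.

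- **From discontinuation:** section 7.1 only, "mortality after 28 days of CRRT discontinuation".
- **From initiation:** the synopsis Method row, which is the summary form of the same design paragraph ("patients mortality within 28 days after CRRT initiation"); the synopsis Validity assessment row ("Mortality within 28 days after initiation of CRRT"); note 7 under both copies of the schedule; 8.2.15; 8.3.4; 11.1.2 ("Mortality at 28 days after initiation of CRRT"); 11.2.2(2); and 11.3.3.2(2) and (6).
- **No origin given:** the synopsis End Point row ("mortality after 28 days after CRRT") and 11.2.2(6) ("We will calculate the survival 28 days after CRRT in both groups").

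On follow-up, note 7 in section 8.1 reads "The patients were followed until discharge for mortality to confirm survival until 28 days after initiation of CRRT". Sections 8.2.15 and 8.3.4 ask for vital status 28 days from initiation. Section 8.3.4 relies on the patient's ordinary outpatient schedule and adds that "no extra-visit for the study is planned".

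On analysis, 11.3.1 limits the ITT set to patients whose vital status is confirmed and allows last observation carried forward. Section 11.3.3.2(6) specifies Kaplan-Meier with censored data included.

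**The concern.** Initiation and discontinuation of CRRT are different kinds of time zero. Initiation lies close to randomisation. Discontinuation follows it, differs between patients (7.1 says so itself), and its timing is analysed as CRRT duration, a secondary outcome in 11.1.2. If the arms differ in CRRT duration, a clock starting at discontinuation gives them windows of different length. It also has no defined start for a patient who dies on CRRT: the text does not say whether such a patient counts as a death or drops out of the comparison. With mortality expected at about 50% (6.3.2), that group may not be small. The trial is open label, so leaving two origins in the text also leaves room to choose between them after results are known.

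The second issue is data collection. A patient discharged alive before day 28 may have no contact at day 28. An analysis plan written later cannot recover vital status that was never collected.

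**Working it through.** **The plan's own figure.** The only computed figure is the sample size in 6.3.2, with α = 0.10, p = 0.50, δ = 0.15 and r = 0.05.

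- n = 1.645² × 0.50 × 0.50 / 0.15² = 30.06, rounded up to 31.
- 31 / (1 − 0.05) = 32.63, rounded up to 33.

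Both figures reproduce. Neither uses the 28-day clock.

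**Two clocks.** The protocol gives no CRRT duration, so 3, 7 and 14 days are assumptions. Mortality at day 28 from initiation is set to 50%, borrowing the 6.3.2 value.

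*Reading A: all deaths up to discontinuation plus 28 days.* With a constant hazard, mortality by day d + 28 is 1 − 0.5^((d+28)/28).

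*Reading B: only patients alive at discontinuation.* Let the hazard be h on CRRT and r·h afterwards, with r = 0.25 or 0.5 (assumed) and h = ln 2 / (d + r(28 − d)). Mortality over the next 28 days is 1 − exp(−28·r·h).

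| CRRT duration d | Window ends (days from initiation) | Reading A | Reading B, r = 0.25 | Reading B, r = 0.5 |
|---|---|---|---|---|
| 3 days | 31 | 53.6% | 40.8% | 46.5% |
| 7 days | 35 | 58.0% | 32.7% | 42.6% |
| 14 days | 42 | 64.6% | 24.2% | 37.0% |

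The initiation clock gives 50% in every row. Under 7.1 the answer moves with d, upwards or downwards according to how deaths on CRRT are handled.

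**Missing day-28 status.** Illustration, not taken from the protocol: one arm of 33, with 15 deaths spread over 28 days (7 before day 14, 8 after). K patients are discharged alive on day 14, all in fact survive, and none has a recorded day-28 status. True mortality is 15/33 = 45.5%.

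- Kaplan-Meier, censored at discharge: survival is 26/33 × (18 − K)/(26 − K), because 26 are alive at day 14, K leave the risk set and 8 of the rest die.
- Left out as unconfirmed (11.3.1, if read as day-28 status): 15/(33 − K).
- Last value carried forward (11.3.1): counted alive, 15/33.

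| K | Kaplan-Meier mortality | Left out | Carried forward |
|---|---|---|---|
| 3 | 48.6% | 50.0% | 45.5% |
| 6 | 52.7% | 55.6% | 45.5% |
| 9 | 58.3% | 62.5% | 45.5% |

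Carrying forward is correct here only because all discharged patients were assumed to live. If some died, it would understate mortality.

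**The case against.** The strongest reply is that 7.1 is one stray sentence. Every endpoint definition and the analysis section that names an origin use initiation, as does the synopsis version of the same paragraph, so an analyst would probably count from initiation anyway. This carries weight on seriousness. It does not remove the contradiction, which sits in the design section and concerns how the groups are compared.

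Several stronger readings are tempting and should be resisted.

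- *The survival analysis also runs from discontinuation.* It does not: 11.3.3.2(6) uses initiation, and 11.2.2(6) is merely silent on the origin.
- *The synopsis as a whole is ambiguous.* Only its End Point row is.
- *Follow-up stops at discharge.* Note 7 taken alone suggests this, but its own purpose is to confirm day-28 survival, and 8.2.15 and 8.3.4 call for that status. Ruling out an extra visit does not rule out a record check or a call.
- *Informative censoring is built in.* Nowhere is a patient censored at discharge. Detailed censoring rules may properly stand in a statistical analysis plan that is not shown, and carrying the last value forward would err in the other direction if it erred at all.

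What survives is narrower: note 7 and 8.3.4 do not agree, and no means of reaching an early-discharged patient at day 28 is fixed.

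**Conclusion.** The point holds for the 28-day mortality endpoint: section 7.1 contradicts the rest of the protocol on time zero, and its version is the poorer one because it starts at a post-randomisation event that is itself an outcome. For CRRT lasting 3 to 14 days the window would end on day 31 to 42 from initiation, and the illustrative mortality moves from 50% to between 53.6% and 64.6%, or to between 24.2% and 46.5% if only patients alive at discontinuation are counted.

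Missing day-28 status after discharge is a conditional risk. If such patients were censored at discharge, Kaplan-Meier survival would be biased downward, by 3 to 13 percentage points in the example (48.6 − 45.5 = 3.1; 58.3 − 45.5 = 12.8). These sizes rest on assumed CRRT durations, hazards and discharge numbers. The protocol gives none of these, so no corrected figure can be stated.

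Only secondary endpoints are touched. ICU mortality, the primary endpoint, and the 31 and 33 per group do not depend on this clock. The correction is worth making, but the point does not undermine the trial's main comparison.

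**What to change.** 1. In 7.1, the synopsis End Point row and 11.2.2(6), count the 28 days from initiation of CRRT, to match 11.1.2.
2. In note 7 (both copies of the schedule), replace follow-up to discharge with vital status at day 28 from initiation for every randomised patient. For those already discharged, obtain it from the hospital record or by one telephone call. Name the same means in 8.3.4, so that it is consistent with having no extra visit.
3. State that survival is censored only at day 28 or at true loss to follow-up, not at discharge.

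The cost is a few wording changes and, for patients who leave before day 28, a short record check or call by existing staff. The sample size, the visits and the primary analysis are unchanged.
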